## Abstract

**Background:**

The choice of surgical or conservative treatment for patients with spontaneous intracerebral hemorrhage is controversial. Some minimally invasive treatments have been applied to hematoma evacuation and could improve prognosis to some extent. Up to now, studies on minimally invasive surgery for patients with spontaneous intracerebral hemorrhage are still insufficient.

**Design:**

The MISTICH is a multi-center, prospective, randomized, assessor-blinded, parallel group, controlled clinical trial. 2448 eligible patients will be assigned to neuroendoscopy group, stereotactic aspiration group and craniotomy group randomly. Patients will receive the corresponding surgery based on the result of randomization. Surgeries will be performed by well-trained surgeons and standard medical treatment will be given to all patients. Patients will be followed up at 7 days, 30 days, and 6 months. The primary outcome of this study is unfavorable outcome at 6 months. Secondary outcomes include: mortality at 30 days and 6 months after surgery; neurological functional status of 6 months after surgery; complications including rebleeding, ischemic stroke and intracranial infection; days of hospitalization.

**Discussion:**

The MISTICH trial is a randomized controlled trial designed to determine whether minimally invasive surgeries could improve the prognosis for patients with spontaneous intracerebral hemorrhage compared with craniotomy. (ChiCTR-TRC-12002026. Registered 23 March 2012).

## Background

Spontaneous intracerebral hemorrhage (sICH) is the most devastate kind of all stokes. It was estimated that sICH affects over 1 million people worldwide every year [1,2]. The case fatality rate of sICH at 30 days is about 30%-55%, and only 12%-39% of the survivors could live independently after 6 months [3-5].

The treatment of sICH is still controversial among neurosurgeons and neurologists. The focus of debate is whether evacuation of hematoma would be able to improve the prognosis of patients. Previous studies showed that the removal of hematoma might reduce nervous tissue damage, possibly by relieving local ischemia and removing noxious chemicals [6-8]. Several studies aiming to explore the efficacy of surgery for patients with sICH have been carried out but showed different results. In 1961, Mickissock and colleagues published the first prospective randomized controlled trial. Their results showed that patients treated surgically had worse outcome than the patients in the conservative group [9]. Another influential study is the STICH series trials, which concluded that there was no overall benefit of early surgery for patients with supratentorial sICH compared with conservative treatment [10,11]. Some researchers attributed this to additional surgical traumatization. In order to reduce surgical traumatization, some minimally invasive techniques have been used in hematoma evacuation. These minimally invasive techniques include stereotactic aspiration and neuroendoscope assisted surgery. The stereotactic aspiration guided by CT was successfully applied for hematoma evacuation by Backlund and collogues at 1978, and this minimally invasive surgery was further improved by some scholars [12]. It was reported that the stereotactic aspiration combined with fibrinolytic drugs could be more effective in hematoma evacuation than aspiration alone [13]. Another category of minimally invasive technique is neuroendoscope. Auer et al. reported that neuroendoscope could be applied to hematoma evacuation, but a subsequent randomized controlled trial showed that the outcome of surgical patients with putaminal or thalamic hemorrhage was not better than medical treatment [14,15]. Recently, a lot of studies exploring the efficacy of minimally invasive surgery (MIS) compared with conservative craniotomy or medical treatment were carried out, but none of them provided sufficient evidence regarding the choice of treatment [16-20]. A further meta-analysis showed that patients with supratentorial intracerebral hemorrhage might benefit more from MIS than other treatment options [21]. Though MIS seems less invasive than the traditional craniotomy, it was reported that the incidence of some complications (e.g. rebleeding and infection) was higher than craniotomy. In addition, with assistance of neuronavigation and operative microscope, hematoma evacuation by craniotomy could also be minimally invasive [22,23]. Until now, there is no randomized controlled trial comparing the efficacy of neuroendoscopy, stereotactic aspiration and craniotomy in patients with spontaneous intracerebral hemorrhage except a small-scale trial by Cho and colleges. Thus, a large-scale clinical trial is necessary to provide robust evidence for clinical practice by assessing the safety and efficacy of different surgical methods including neuroendoscopy, CT-stereotactic aspiration and neuronavigation-assisted craniotomy for sICH. Here we designed a randomized, assessor-blinded, parallel-group, controlled, multi-center clinical study termed minimally invasive surgery treatment for patients with spontaneous supratentorial intracerebral hemorrhage (MISTICH).

## Design

The MISTICH is a multi-center, prospective, randomized, assessor-blinded, parallel group, controlled clinical trial. The overall flow of MISTICH is showed in Figure 1. A total of 20 centers from around China are included. The centers were eligible if they: have the ability to carry out all kinds of minimally invasive surgery of this trial; demonstrate adequate trial experience; have previous adherence to trial guidelines with high follow-up rates. All participating hospital sites are to receive approval from the relevant ethics committee before initiation of the study. Until now, 20 centers are currently involved with this study and all of the centers have already received ethical approval. This study has been registered in the Chinese Clinical Trial Registry (ChiCTR-TRC-12002026). All the patients or their legal surrogate will be fully informed and informed consent will be signed in this trial.

**Figure 1 Fig1:**
[figure not shown]
**Flow diagram of the MISTICH study.**

### Study objective

The primary objective is to evaluate different minimally invasive techniques including neuronavigation assist craniotomy, neuroendoscopy, and CT-stereotactic aspiration on their unfavorable outcomes at 6 months in patients with spontaneous intracerebral hemorrhage. The secondary objective is to investigate the safety of different minimally invasive techniques. Another objective is to evaluate the separate effects of treatment on death and dependency through physical function, complications, and days of hospitalization.

### Patient population

#### Inclusion criteria

Age between 15 and 75 years;Diagnosed with acute spontaneous supratentotial intracranial hemorrhage (Meets U.S. adults spontaneous intracerebral hemorrhage treatment guidelines (2010) diagnostic criteria)Within 48 hours post ictus;With Glasgow Coma Scale (GCS) between 5 and 12;CT scan showed hematoma volume is 30 ml or above;Agree to participate in this clinic trial and sign the informed consent.

#### Exclusion criteria

The intracerebral hemorrhage is caused by secondary factors (e.g. arteriovenous malformation; aneurysm; tumor stroke);Concurrent head injury or history of head injury;Multiple intracranial hemorrhage;Known advanced dementia or disability before ICH happened;With coagulation disorders or history of anticoagulant drugs;With severe liver or kidney dysfunction;With indications of terminal brain hernia (e.g. bilateral mydriasis and loss of light reflex, serious disorders of the vital signs);Pregnancy;With severe intraventricular hemorrhage (CT scan shows that volume of hematoma in the lateral ventricular is over 1/2 of ventricluar), or lateral ventricular enlarge with third and fourth ventricular hematoma.

### Sample size

It was reported that the rate of poor outcome of patients with a hemorrhage volume above 30 ml who received craniotomy is about 49% to 67% [19,21,24]. Previous studies showed that the MIS could decrease the rate of poor outcome by about 7% to 22% [19,21] compared with craniotomy. We assume that the neuroendoscopy and stereotactic aspiration can reduce the rate of poor outcome from 58% to 51%, and a sample size of 2203 patients will be required with a significance level of 5% (2-sided) and a power of 80%. In consideration of ensuring the quality of research, the sample size is enlarged to 2448 (816 In each arm).

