### Statistical analysis

The “intension to treat” analysis will be applied in this study. The descriptive analysis of all measurement data is implemented using mean, standard deviation, median, interquartile range, maximum and minimum indicators; the descriptive analysis of count data is implemented using index such as rate, ratio and RR. The primary analysis will be a simple categorical frequency comparison for unfavorable outcome by means of Chi-square test, so will the categorical data of secondary outcomes. The continuous outcomes will be analyzed by t-test. The log-rank method will be used in the analysis of time- to-event type of outcomes. Subgroup analysis stratified by age, location of hematoma, volume of hematoma, GCS at hospitalization, with/without intraventricular hemorrhage, and midline shift is preplanned. Statistical inference is conducted using the above-mentioned hypothesis testing method and confidence interval may also be used when necessary. P values ≤0.05 (α = 0.05) will be considered statistically significant. All statistical analysis is performed using SAS or SPSS statistical software.

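### The 80% power at 2203 patients fits a three-arm overall test, not the comparison of each minimally invasive arm with craniotomy; at the planned size that comparison can have about 81% power or error control, but not both

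*Protocol article*

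**What the plan says.** Four places in the protocol article bear on this point.

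- **Sample size.** The effect assumption is: "We assume that the neuroendoscopy and stereotactic aspiration can reduce the rate of poor outcome from 58% to 51"%. From it the article concludes that "a sample size of 2203 patients will be required with a significance level of 5% (2-sided) and a power of 80"%. Then "the sample size is enlarged to 2448 (816 In each arm"); the only reason given is "In consideration of ensuring the quality of research". No test, contrast or dropout rate is named.
- **Statistical analysis.** "The primary analysis will be a simple categorical frequency comparison for unfavorable outcome by means of Chi-square test". One threshold covers everything: "P values ≤0.05 (α = 0.05) will be considered statistically significant". The section gives no degrees of freedom, no pairwise contrasts of the primary outcome, no order of testing and no division of alpha.
- **Abstract, Discussion.** The trial is "designed to determine whether minimally invasive surgeries could improve the prognosis for patients with spontaneous intracerebral hemorrhage compared with craniotomy".
- **Study objective.** The primary objective is to "evaluate different minimally invasive techniques including neuronavigation assist craniotomy, neuroendoscopy, and CT-stereotactic aspiration", so craniotomy appears among the techniques under evaluation and no contrast is named.

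**The concern.** With three arms, a chi-square test of unfavorable outcome by treatment has 2 degrees of freedom. A significant result says that the three rates are not all equal. It does not say which arm differs or in which direction. The question in the abstract is directional and has a reference arm, so it needs comparisons with craniotomy.

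Two things are at stake. First, a reader will take the stated 80% as the chance of showing that neuroendoscopy, or stereotactic aspiration, beats craniotomy; if the figure belongs to the overall test, it does not carry over. Second, the step from a significant overall result to a claim against craniotomy is not described, and the only rule given is P≤0.05 for every test. If pairwise tests are read at that threshold with nothing ahead of them, the chance of at least one false claim exceeds 5%.

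**Working it through.** **Inputs.** Rates 0.58, 0.51, 0.51; two-sided alpha 0.05; power 80%; N = 2203 (734.3 per arm); planned N = 2448 (816 per arm). All are from the Sample size section.

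**1. Reproduce 2203.** For a 3×2 Pearson chi-square with equal arms:

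- mean rate = (0.58 + 0.51 + 0.51)/3 = 0.5333
- w² = mean of (pᵢ − 0.5333)² / (0.5333 × 0.4667) = 0.0010889 / 0.248889 = 0.004375
- noncentrality for 80% power at 2 df and alpha 0.05 = 9.635
- N = 9.635 / 0.004375 = 2202.2, so 2203

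The match is exact. Power of this test is 80.0% at 2203 and 84.3% at 2448.

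**2. Try the alternatives** (three-arm totals, 80% power):

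| Calculation | Per arm | Total |
|---|---|---|
| Pairwise, 5% two-sided | 794 | 2382 |
| Same, continuity-corrected | 822 | 2466 |
| Pairwise, 5% one-sided | 625 | 1875 |
| Pairwise, Bonferroni for two | 961 | 2883 |
| Pairwise, Bonferroni for three | 1059 | 3177 |
| Both minimally invasive arms pooled vs craniotomy | 596 | 1788 |

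None gives 2203. The nearest figure, 2174, is a two-arm total (2 × 1087, Bonferroni for three with continuity correction) and does not fit a three-arm trial.

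**3. Power for one minimally invasive arm against craniotomy.** With n per arm and pooled rate 0.545:

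power = Φ{[0.07√n − z(1−α/2)·√(2 × 0.545 × 0.455)] / √(0.58 × 0.42 + 0.51 × 0.49)}

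- n = 734.3, α = 0.05: (1.8969 − 1.3803)/0.7025 = 0.735, so 76.9%
- n = 816, α = 0.05: (1.9996 − 1.3803)/0.7025 = 0.882, so 81.1%

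The other unadjusted and Bonferroni figures use the same formula. The gated figures come from simulation (300,000 trials per setting), with the 2-df test required to be significant at 5% before the pairwise test at 5%.

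| Rule | 734 per arm | 816 per arm, no loss |
|---|---|---|
| Unadjusted 5% | 76.9% | 81.1% |
| After a significant overall test | 72% | 77% |
| Bonferroni for two | 67.5% | 72.6% |
| Bonferroni for three | 61.8% | 67.2% |

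The chance of showing both minimally invasive arms better under the gate is about 64% at 734 and 70% at 816 per arm.

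**4. Margin at 816 per arm.** Unadjusted 80% power needs 794 per arm. 816 − 794 = 22, and 22/816 = 2.7%. Beyond that proportion of missing outcomes, even the unadjusted comparison is below 80%.

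**5. False-positive risk when all three rates are equal** (same simulation, all rates 58%): about 9.0% for at least one significant result among the two comparisons with craniotomy, and about 12.1% among all three pairs, each at 5% without a gate. With the overall test as gate, it is about 5%.

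**6. The enlargement.** 2203/0.90 = 2447.8, so 2448 matches a 10% loss allowance. The article does not say so; this is an inference.

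**The case against.** The strongest reply is that the article agrees with itself. If the primary test is the 2-df chi-square, then the sizing, the single primary chi-square test and an objective that evaluates three techniques all fit together, and the primary test has a type I error of 5%. Follow-up contrasts and multiplicity rules are commonly left to an SAP, which is not shown, and this is a condensed article. Much of this stands: the absence of a gate from the article does not show that the trial has none. What remains is that the 80% is attached to a test that does not answer the abstract's question, and that the article does fix one threshold for all tests.

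Some stronger readings are tempting but not supported:

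- *That the pairwise comparisons lack 80% power altogether.* At 816 per arm, an unadjusted 5% and complete outcomes, power is 81.1%.
- *That the false-positive risk is more than doubled.* The 9% and 12% arise only if ungated pairwise tests decide the trial, and the article names no pairwise test of the primary outcome. The 12% also needs the comparison between the two minimally invasive arms, which the abstract does not ask for.
- *That only 2203 patients will be evaluable.* No loss rate is stated.
- *That the comparator is never fixed.* The abstract names craniotomy as the reference, and the Sample size section sets the other two arms against its rate. Only the Study objective blurs this.

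One could also read the abstract as asking about both minimally invasive arms pooled. That contrast would have 87.5% power at 2203 and 90.7% at 2448. But neither the Sample size nor the Statistical analysis section mentions pooling, and 2203 does not come from it.

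**Conclusion.** The point holds in a limited form. The 80% at 2203 patients is the power of an overall three-arm test, as inferred from an exact numerical match. It is not the power of a comparison between one minimally invasive arm and craniotomy, which is 76.9% at that size even with no adjustment. That shortfall does not depend on the inference about the test.

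At the planned 816 per arm there is a choice: about 81% pairwise power with no control across comparisons and under 2.7% missing outcomes, or control of the family-wise error with about 77% (overall-test gate) or 67–73% (Bonferroni). Both cannot be had at 80%. These figures assume the article's own rates of 58% and 51% and equal arms. Bonferroni is shown for illustration and is slightly conservative for correlated comparisons.

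A reader might conclude that the trial is too small and must grow. The documents do not support that: the overall test is adequately powered, and the gated pairwise power is moderately below 80%. What needs correcting is the claim attached to the figure and the route from the overall test to the conclusion.

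**What to change.** Keep the sample size and change three sections, before any comparison of outcomes by arm is seen.

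1. **Statistical analysis.** State a closed procedure: the 2-df chi-square test at 5% first; only if it is significant, each minimally invasive arm against craniotomy and the two minimally invasive arms against each other, each at 5%. With three arms this holds the family-wise error at 5% without splitting alpha: if all three rates are equal, the gate gives 5%; if only two are equal, just one true null hypothesis remains, and it is tested at 5%. If the SAP already contains such a rule, cite it here.
2. **Sample size.** Say that 80% at 2203 (84% at 2448) is the power of the overall test. Add the power for each minimally invasive arm against craniotomy under the gate: about 77% at 816 per arm, or about 72% at 734 per arm if about 10% are lost, with that loss rate stated as an assumption.
3. **Study objective.** Name craniotomy as the comparator, in line with the abstract and the Sample size section.

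The cost is wording only, with no extra patients. The drawback is that the stated power for the individual comparisons becomes less favorable. If the sponsor wants 80% for each comparison with Bonferroni for two, the total would be 2883 before any allowance for loss.

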### Randomization

Patients will be allocated to neuroendoscopy group, stereotactic aspiration group and craniotomy group by method of simple randomization. The randomized number was created before the trial by SPSS 19.0 and kept in envelopes. The envelopes within randomized number will be sent to the centers before trial begin.

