### Blinding

It was impossible to blind either the treating doctors or patients in this trial. In order to ensure the quality of this research, the assessors will be blinded. The outcomes of patients will be measured and filled in paper Case Reports Froms (CRF) by special researchers who would not take part in the allocation and the treatment.

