### Treatment

After eligible patients are admitted to the hospital, the investigator will collect the basic information of patients, sign the informed consent and identify the randomized assignment as soon as possible. For all the patients, best medical treatments followed the recommendation of 2010 ASA/AHA intracerebral hemorrhage guidelines and preoperational preparation will be conducted at the same time. The patients will receive the corresponding surgery based on the result of randomization. All the surgeries will be performed as soon as possible after the randomization.

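### All allocation envelopes are held at the centres, where unblinded staff enrol patients and read the assignment, so allocation could be known or steered at site; balance within centre is also uncontrolled

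*Protocol article*

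**What the plan says.** The Randomization section of the protocol article fixes three things. The method: "Patients will be allocated to neuroendoscopy group, stereotactic aspiration group and craniotomy group by method of simple randomization". The carrier: "The randomized number was created before the trial by SPSS 19.0 and kept in envelopes". The place where allocations wait: "The envelopes within randomized number will be sent to the centers before trial begin".

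The Blinding section adds "It was impossible to blind either the treating doctors or patients in this trial". It keeps the outcome assessors apart from allocation and treatment, but states no such separation between enrolment and allocation. The Treatment section has the investigator collect baseline information, then "sign the informed consent and identify the randomized assignment as soon as possible".

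On size, the Design section says "A total of 20 centers from around China are included", and the Sample size section says "the sample size is enlarged to 2448 (816 In each arm)". The Statistical analysis section names a plain chi-square test for the primary outcome, on an intention-to-treat basis, with no term for centre.

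**The concern.** The arms are three visibly different operations, and local staff may prefer one of them for a given patient. Every future allocation is physically at the site. The person who has just seen the patient's age, GCS and hematoma volume also finds out the assignment. If an envelope can be read early, passed over or exchanged, patients with better or worse prospects can be directed to a chosen arm.

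That would be selection bias at entry. Blinded assessors would measure the outcome correctly in groups that were not comparable, and intention-to-treat analysis would preserve those groups as they stand. A larger sample would not shrink the bias; it would only make it look more precise.

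A second, smaller matter is balance. Simple randomization gives equal arms only in expectation and does nothing to even out arms within a centre, while the stated test leaves centre out.

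**Working it through.** **1. The plan's own sample size.** Inputs from the Sample size section: 58% against 51% in each of the other two arms, two-sided 5%, 80% power. For a 3×2 chi-square test with 2 df:

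- mean rate = (0.58 + 0.51 + 0.51)/3 = 0.5333
- sum of squared deviations = 0.003267
- divided by 0.5333 × 0.4667 = 0.2489, this gives 0.013125 per patient per arm
- noncentrality needed for 80% power = 9.635
- n = 9.635/0.013125 = 734.07 per arm, or 2202.2 in total, which agrees with the stated 2203

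2203/0.90 = 2447.8, so 2448, and 2448/3 = 816. The 10% enlargement is inferred; the article does not state it. The sample size figure is not in dispute.

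**2. Overall arm size under simple randomization.** SD = √(2448 × 1/3 × 2/3) = 23.3, and 816 ± 1.96 × 23.3 = 770 to 862. The chance of exactly 816 in all three arms is 0.034%. Effect on power for a pairwise comparison of 58% with 51%:

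| Arm sizes | Power |
|---|---|
| 816 and 816 | 81.10% |
| average over simple randomization | 81.07% |
| 770 and 816 | 79.9% |

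Even 770 exceeds the 734 behind the 2203.

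**3. Arm size within a centre.** Assumption: the 20 centres recruit equally, so 2448/20 = 122.4 each. Expected arm size = 40.8; SD = √(122.4 × 2/9) = 5.2; 40.8 ± 10.2 = 31 to 51. By simulation with 122 patients per centre, the gap between the largest and smallest arm has median 10 and 95th percentile 21, and is at least 10 in 55% of centres. In the worst of 20 centres its median is 22.

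**4. What steering could do.** The article gives no rate of steering and no risks by patient type, so this is a range of assumptions. Let f be the share of an arm's allocations exchanged, all in one direction, and g the difference in risk of poor outcome between the patients exchanged. One arm moves by f × g. If the exchange is between the two arms being compared, their difference moves by 2 × f × g. With 816 per arm and 58% in both, the SE of a difference is √(2 × 0.58 × 0.42/816) = 2.44 points. The false-positive rate follows from shifting a normal statistic by bias/SE.

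| f | g (points) | One arm moves (points) | Two-sided false-positive rate | Both arms move (points) | Two-sided false-positive rate |
|---|---|---|---|---|---|
| 1% | 20 | 0.2 | 5.1% | 0.4 | 5.3% |
| 1% | 45 | 0.45 | 5.4% | 0.9 | 6.6% |
| 5% | 20 | 1.0 | 6.9% | 2.0 | 13.0% |
| 5% | 45 | 2.25 | 15.1% | 4.5 | 45.3% |

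The target difference is 58 − 51 = 7 points. Steering in opposite directions at different centres would partly cancel, so these are figures for consistent steering.

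**The case against.** The best defence is that the Randomization section is a three-sentence condensation. Sealing, opacity, sequential numbering and a log of opened envelopes are details that an article leaves to the full protocol. That stands: a reader might infer that nothing binds an envelope to a patient, but the article does not show this. Nor does it say that the investigator who identifies the assignment is the operating surgeon, or chooses among envelopes. The Treatment section also lists baseline data and consent before the assignment. What remains is the stated choice to keep the whole list at the sites. Good envelopes make tampering harder, but the allocations are still in local hands.

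A reader might also infer that simple randomization lets staff foresee the next arm. It does not: past allocations say nothing about the next one, and any foresight comes through the envelopes alone. Centre-stratified blocks would in fact make some allocations easier to guess in an open trial.

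On balance, the defence is largely right. The 816 per arm reads naturally as a target, and missing it costs almost nothing. Chance imbalance by centre does not bias a simply randomized comparison, and the chi-square test stays valid without a centre term. The article does not say that skill or case mix differs by centre, and the Design section admits only centres able to perform all the minimally invasive procedures.

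**Conclusion.** The concern holds for concealment. Site-held envelopes, unblinded treating staff and a single local role for consent and assignment leave a route to selection bias that the other safeguards in the article cannot close. Nothing in the article shows that steering has happened or would happen. Its possible size, 0.2 to 4.5 points against a 7-point target, rests wholly on the assumed shares and risk gaps; no single figure from that range should be quoted as the expected bias.

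The balance part is secondary. It would go too far to read the 816 per arm as a loss of power or the chi-square test as invalid. What can be said is that 816 is an expected size under the stated method, that balance within centre is uncontrolled (about 31 to 51 per arm under equal recruitment), and that using centre in the analysis would gain precision if outcome differs between centres.

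**What to change.** 1. Hold the allocation list centrally. Release each assignment by telephone or web form only after eligibility and consent have been logged against a patient number.
2. For any patients already randomized from envelopes, check envelope order against enrolment order at each centre and report discrepancies.
3. In the Sample size section, describe 816 as the expected number per arm. If the list was in fact forced to 816 each, the Randomization section should not call it simple randomization.
4. Adjust the primary comparison for centre, for example by Mantel-Haenszel or logistic regression with centre as a factor.
5. Centre-stratified permuted blocks of varying size are optional, and advisable only once release is central. With envelopes at the sites they would add predictability.

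The cost is an amendment and a release service that can be reached out of hours, since patients enter within 48 hours of onset and surgery follows as soon as possible. No additional patients are needed.
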